### Surveillance and follow-up

All participating hospitals use the same electronic case report form (eCRF) available at REDCap system to collect data of patients. All centers participating in the trial, ethics committee, and statisticians will have access to the system. Patients’ identity information is encrypted to prevent leakage. An independent data monitoring committee is responsible for summarizing and checking the data of each center. Moreover, if they have any questions, they can contact the co-investigators of each center to review or revise. Both the rivaroxaban group and the control group will be followed at 1, 3, 6, 12, 18, and 24 months after the operation. Once bleeding, thromboembolism, or other adverse events occur, patients need to report to the hospital immediately. The schedule of enrolment, interventions, and assessments is shown in Fig. 2.

**Fig. 2 Fig2:**
[figure not shown]
Schedule of enrolment, interventions, and assessments

### Outcome measures

The primary outcome of the study is stent occlusion rate. The occlusion of stent will be confirmed by DUS and CTV. Stent occlusion is defined as DS > 50% for each modality with no procedure performed on the treated segment [19]. The secondary outcomes consist of quality of life scale survey results, all-cause mortality, anticoagulation-related mortality, and the proportion of participants with stent displacement/fracture, thrombosis, hemorrhage, and other vascular events. Quality of life will be assessed by MOS item short-form health survey scale (SF-36). SF-36 includes eight subscales: physical functioning (PF, ten items), role limitations due to physical health problems (RL-P, four items), bodily pain (BP, two items), general health (GH, five items), vitality (V, four items), social functioning (SF, two items), role limitations due to emotional problems (RL-E, three items), and mental health (MH, five items) [20]. Computed tomography (CT) will be used to detect stent displacement/fracture. Diagnosis of thrombosis will be based on color Doppler ultrasound and D-Dimer. Hemorrhage includes hemorrhagic stroke, gastrointestinal bleeding, hematuria, mucocutaneous hemorrhage, and another visceral bleeding. The diagnosis of hemorrhage will be based on clinical history, symptoms, laboratory examination, and imaging findings. For example, hematuria will be diagnosed according to the results of urinalysis. Moreover, the diagnosis of vascular events, including acute coronary syndrome, ischemic stroke, pulmonary embolism, transient ischemic stroke, and other parts of vascular embolism, will depend on CT/MRI.

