### Sample size calculation

According to Snyder et al., stent occlusion rate of thrombotic LIVCS was 20.2% [21]. For the noninferiority test of group design, 202 cases recruited in the study are enough under the power of 0.8, two-sided alpha level of 0.05, and the non-inferiority margin of 0.1. We will include 224 samples in the study, taking into account a dropout rate of 10%, 112 in the experimental group, and 112 in the control group.

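### The primary event requires that no procedure was done on the treated segment, so read literally a failed stent that is re-treated before being recorded is not counted

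*Protocol article*

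**What the plan says.** The Outcome measures section makes stent occlusion the primary outcome ("The primary outcome of the study is stent occlusion rate"), requires two imaging methods ("The occlusion of stent will be confirmed by DUS and CTV"), and then gives the only definition of the event: "Stent occlusion is defined as DS > 50% for each modality with no procedure performed on the treated segment".

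The secondary outcomes in the same section are quality of life, all-cause and anticoagulation-related mortality, and "the proportion of participants with stent displacement/fracture, thrombosis, hemorrhage, and other vascular events". Re-intervention on the stent is not among them.

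The Sample size calculation section plans a non-inferiority test on a control rate of 20.2% with "the non-inferiority margin of 0.1", "two-sided alpha level of 0.05" and 112 patients per arm. The Statistical analysis section specifies intention to treat, an uncorrected chi-square test for binary outcomes followed by a Cox model, and log-rank and Kaplan-Meier methods for survival differences. Treatment is open-label with blinded assessors and a blinded adjudication committee. Follow-up runs to 24 months.

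**The concern.** A no-procedure condition belongs naturally to patency, meaning a vessel that stays open without help. Here it is attached to the failure event. The sentence then sets two joint conditions: stenosis above 50% on each modality, and no procedure on the segment. A stent that narrows or thromboses and is re-opened before it is recorded fails the second condition. Nothing in the article says that re-intervention is an event, is censored, or is handled in any other way. Under intention to treat, such a patient is analysed as having no primary event.

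In a non-inferiority trial, losing a similar share of failures in both arms pulls the arms together and makes a false claim of non-inferiority easier. Treating doctors also know the arm, as the Discussion acknowledges. If they decide on re-intervention, the primary result depends partly on unblinded decisions. Blinded adjudication does not help if the definition it applies excludes the event.

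**Working it through.** **The plan's own figure.** The article gives no figure for re-treatment, so there is nothing to reproduce on that point. Its total of 202 before dropout does not follow from its stated inputs: 2 × 0.202 × 0.798 × (1.960 + 0.842)² / 0.10² is just over 253, or 254 per arm after rounding up. That is a separate matter. The check below takes 112 per arm as given.

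**Inputs from the protocol article (Sample size calculation).** Control rate 0.202; margin 0.10, taken as an absolute difference; two-sided alpha 0.05; 112 per arm.

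**Assumptions, not in the article.**
- The true rivaroxaban rate is 0.302, worse by exactly the margin, so any claim of non-inferiority is false.
- A share *r* of failures is re-treated, and every one of them is lost from the count.
- Non-inferiority is claimed when the upper limit of the 95% confidence interval for the difference is below 0.10. The article does not state this criterion; it is the usual counterpart of the stated margin and alpha.

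**Formulas.**
- Counted rate in each arm = true rate × (1 − *r*).
- d = p_R − p_W, where p_R and p_W are the counted rates on rivaroxaban and warfarin.
- SE = √{[p_R(1 − p_R) + p_W(1 − p_W)] / 112}.
- P(claim) = Φ((0.10 − d)/SE − 1.96).

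**Same share in both arms.**

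| Share re-treated | Rivaroxaban | Warfarin | d | SE | P(claim) |
|---|---|---|---|---|---|
| 0% | 0.3020 | 0.2020 | 0.100 | 0.0576 | 2.5% |
| 10% | 0.2718 | 0.1818 | 0.090 | 0.0556 | about 4% |
| 25% | 0.2265 | 0.1515 | 0.075 | 0.0521 | 6.9% |
| 50% | 0.1510 | 0.1010 | 0.050 | 0.0442 | about 20% |

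For the 25% row: (0.10 − 0.075)/0.0521 − 1.96 = 0.480 − 1.96 = −1.480, and Φ(−1.480) = 0.069.

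**Different shares by arm.**

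| Re-treated, rivaroxaban v warfarin | Rivaroxaban | Warfarin | d | SE | P(claim) |
|---|---|---|---|---|---|
| 40% v 20% | 0.1812 | 0.1616 | 0.0196 | 0.0503 | 35.8% |
| 20% v 40% | 0.2416 | 0.1212 | 0.1204 | 0.0509 | 0.9% |

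**Sensitivity to dropout.** With 101 per arm (half of 202), the three non-zero same-share rows become 3.7%, 6.6% and 18.8%, so the choice of denominator matters little.

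**The case against.** The strongest objection is that the clause may only fix timing: stenosis above 50% seen on a segment not yet re-treated. A stent confirmed as failed and then re-opened would already have had its event. Patients are told to report thromboembolism at once, a committee adjudicates all events, and the planned log-rank and Cox methods suit a first-event analysis. This stands in part. A reader might infer that every re-treated failure is scored as a success, and the article does not establish that. On the timing reading, only failures re-treated before both images were obtained would be lost, and the tables above are then upper-end figures for each share. But the article does not state the timing reading, does not tie the survival methods to stent occlusion, and also plans a binary comparison.

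Four other inferences go too far:
- **That lost events always favour non-inferiority.** The 20% v 40% case widens the difference to 12 points and lowers the false-claim rate to 0.9%. Nothing in the article says which arm would be re-treated more.
- **That the 20.2% planning rate describes a different event.** It comes from a cited source that is not available here. Calling stenosis above 50% an occlusion is a label the protocol defines openly, not a contradiction.
- **That the re-treated failures vanish from the trial.** Some may appear under the secondary outcome of thrombosis, though not in the primary outcome.
- **That re-interventions are already captured.** The article lists no eCRF fields.

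**Conclusion.** The concern holds in a limited form. As worded, the definition lets a failed stent that is re-treated before being recorded go uncounted, and no other part of the article corrects this. It is a stated rule that can give a wrong primary result, not merely an omitted detail, so it should be corrected even if the timing reading was intended.

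The size is conditional. With equal re-treatment of 10% to 50% and all such failures lost, the false non-inferiority rate goes from 2.5% to between about 4% and 20%. With unequal re-treatment it could be as high as about 36% or as low as about 1% in the cases shown. The shares, the complete loss of re-treated failures and the confidence-limit criterion are all assumptions. The direction of bias is predictable only when re-treatment is similar in the two arms.

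**What to change.** Define the primary event as adjudicated diameter stenosis above 50% on the stented segment, or any re-intervention for stenosis or occlusion of that segment, whichever comes first. Report the two components separately. Have the blinded committee adjudicate the reason for each re-intervention, since the decision itself is made open-label. Make sure the eCRF records re-interventions with date and indication.

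The cost is a short change to the protocol and registry entry, matching instructions for the adjudication committee, and an eCRF field if none exists. The article reports that recruitment had not started, so the change could be made before outcome data accrue.

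The downside is that the counted event rate may rise, and not necessarily by a little. If 25% or 50% of failures would otherwise be lost, restoring them multiplies the counted rate by 1/0.75 = 1.33 or 1/0.50 = 2. The 20.2% planning rate should therefore be checked against the revised definition, and the sample size revisited if they differ.

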## Methods

### Study design and setting

The study is a prospective, randomized, multicenter, controlled trial that will evaluate the efficacy and safety of rivaroxaban for the prevention of deep vein thrombosis in patients with left iliac vein compression syndrome treated with stent implantation. The ethics committee approved the study at each participating hospital and written informed consent will be obtained from patients before enrolment. Doctors in charge of each center is responsible for this work. The independent adjudication committee blinded to the intervention will adjudicate all events. We will randomly allocate patients to either the experimental group or the control group after enrollment. The study was registered in the website of ClinicalTrials.gov (registration no. NCT04067505). And the study design is described in Fig. 1.

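### CT/MRI is the only diagnostic basis named for the secondary outcome of other vascular events; it does not suit acute coronary syndrome or transient ischaemic events and may under-count them

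*Protocol article*

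**What the plan says.** The secondary outcomes, listed in the protocol article under Outcome measures, include "all-cause mortality, anticoagulation-related mortality, and the proportion of participants with stent displacement/fracture, thrombosis, hemorrhage, and other vascular events". The last item is then given its diagnostic basis in one sentence, under which the diagnosis of vascular events such as "acute coronary syndrome, ischemic stroke, pulmonary embolism, transient ischemic stroke, and other parts of vascular embolism, will depend on CT/MRI". No symptom, ECG, laboratory or clinical criterion is attached to any event on that list.

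The same section treats bleeding differently: "The diagnosis of hemorrhage will be based on clinical history, symptoms, laboratory examination, and imaging findings", with urinalysis as a worked example for haematuria.

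Two other statements bear on the point. Under Study design and setting: "The independent adjudication committee blinded to the intervention will adjudicate all events". Under Surveillance and follow-up: "Once bleeding, thromboembolism, or other adverse events occur, patients need to report to the hospital immediately"; patients in both groups "will be followed at 1, 3, 6, 12, 18, and 24 months after the operation".

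**The concern.** A diagnostic basis in an outcome definition decides which patients count as having the event. Here a single imaging basis is set for a list whose members are not all imaging diagnoses. A patient with typical chest pain, ECG changes and raised troponin, but no CT or MRI, does not meet the stated basis. Nor does a patient with a classic transient neurological deficit and a clean scan.

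At stake is the completeness of one secondary outcome. If these events are left out, the reported proportion with other vascular events is too low. If some sites or adjudicators follow the sentence literally and others use ordinary clinical criteria, the count means different things across the 9 hospitals.

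**Working it through.** The article gives no figure for this outcome to reproduce: no expected vascular event rate and no power statement. The only sample size statement, "202 cases recruited in the study are enough under the power of 0.8, two-sided alpha level of 0.05, and the non-inferiority margin of 0.1", is built on stent occlusion. The check is therefore a reading of the text.

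**Step 1. Does the stated basis fit each listed event?** The left column comes from Outcome measures. The right column is general clinical knowledge, which the article does not state, and is taken here as an assumption.

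| Event on the list | Does CT/MRI suit it as the diagnostic basis? |
|---|---|
| Ischaemic stroke | Yes |
| Pulmonary embolism | Yes |
| Other vascular embolism | Yes |
| Acute coronary syndrome | No. Established from symptoms, ECG and cardiac biomarkers; CT or MR can support it but does not define it, least of all in unstable angina |
| Transient ischaemic event (the article calls it a stroke; read here as a transient ischaemic attack) | No. A clinical diagnosis, often with no lesion on imaging |

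Four specific types and one residual category are named. The basis fails for two of the four specific types.

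**Step 2. Is the imaging wording a real restriction or loose shorthand?** The bleeding sentence in the same section lists four sources: history, symptoms, laboratory tests and imaging. The authors named several sources where they meant several. The vascular sentence names imaging alone. The natural reading is that imaging decides, although the sentence does not say that it is the sole criterion.

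**Step 3. Does another provision supply the missing criteria?** Prompt reporting and the visit schedule bring events to the hospital's notice but do not say what counts as one. The committee decides what counts, but the only vascular event criterion in the article is the CT/MRI one. Faced with a biomarker-positive patient who had no scan, it must either reject the event or set the stated basis aside.

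**Step 4. Can the loss be sized?** For one arm, expected events lost = n × p × s. Here n = 112 (Sample size calculation), p is the true proportion with acute coronary syndrome or a transient ischaemic event, and s is the share of those that imaging would not confirm. The article gives neither p nor s. Since s can lie anywhere from 0 to 1, the loss runs from none of these events to all of them, and the documents do not narrow that range.

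**Step 5. What would the loss do to the comparison?** If s is the same in both arms, the observed difference for these two components is (1 − s) × (p₁ − p₂). It keeps its sign and shrinks towards zero. The article does not show that s would differ between arms.

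**The case against.** The strongest reply is that the sentence says diagnosis depends on imaging, not that it rests on imaging alone, and that nothing in the article says an event without a positive scan is discarded. All events go to a blinded committee, which can be expected to use clinical sense. The article is also a condensed account: detailed bleeding definitions are placed in the Supplementary Appendix, and fuller vascular definitions may sit in the full protocol or an adjudication charter.

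Much of this stands. It limits the conclusion to possible under-counting, and it means that absent detail is not in itself a fault. It does not remove the point, because the article states a basis, and that basis is unsuitable for part of its own list. The committee has no other stated criterion to apply.

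Three stronger readings are tempting and are not supported:

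- **Fatal events are lost to the trial.** A reader might infer this for a death from suspected pulmonary embolism before any scan. All-cause mortality is a separate secondary outcome, so the death is counted there. What the article leaves unstated is only whether it also enters the vascular event proportion.
- **Pulmonary embolism is in the wrong group.** A reader might note that the trial is to "evaluate the efficacy and safety of rivaroxaban for the prevention of deep vein thrombosis" and want pulmonary embolism reported with thrombosis. The stated aim names deep vein thrombosis, and the grouping matches the diagnostic methods (ultrasound and D-dimer for thrombosis, CT/MRI for pulmonary embolism). Nothing prevents separate reporting. This is a reporting preference, not an error.
- **The bias is known in size or favours one drug.** The article gives no event rates and applies one rule to both arms.

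**Conclusion.** The point holds in a limited form. The article names CT/MRI as the only diagnostic basis for every component of other vascular events. That basis does not suit acute coronary syndrome or transient ischaemic events, and applied as written it may under-count both. The extent cannot be calculated from the documents.

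The conclusion rests on three assumptions: that the transient ischaemic entry means a transient ischaemic attack; that the two diagnoses are made clinically, as set out in the working; and that no fuller definition elsewhere overrides the sentence. If such a definition exists, the article's sentence should be brought into line with it.

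The reach is modest: two components of one of several secondary outcomes. The primary outcome, the non-inferiority margin and the sample size are unaffected. The correction is still worth making because the sentence is a positive rule that sites and adjudicators could follow literally.

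**What to change.** Replace the single sentence with a basis for each component:

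- **Acute coronary syndrome:** classified from symptoms, ECG and cardiac biomarkers.
- **Transient ischaemic event:** an adjudicated clinical transient deficit, with imaging used to exclude infarction or bleeding. Name it as a transient ischaemic attack if that is what is meant.
- **Ischaemic stroke, pulmonary embolism and other embolism:** CT/MRI, as now.
- **Suspected fatal events without imaging:** classified by the existing blinded adjudication committee from the available records.

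Add eCRF fields so that the committee receives the symptoms, ECG and biomarker results.

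The cost is protocol and eCRF wording and slightly more adjudication work. No treatment, visit or sample size changes. The Trial status section says that recruitment had not started, so at that stage the change could precede the first event. If enrolment has since begun, the committee can apply the revised definitions to events already recorded, blinded to treatment group, with the date of the change documented.

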### Sample size calculation

According to Snyder et al., stent occlusion rate of thrombotic LIVCS was 20.2% [21]. For the noninferiority test of group design, 202 cases recruited in the study are enough under the power of 0.8, two-sided alpha level of 0.05, and the non-inferiority margin of 0.1. We will include 224 samples in the study, taking into account a dropout rate of 10%, 112 in the experimental group, and 112 in the control group.

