**Methods:**

This study is a multicenter, randomized controlled trial. We will recruit 224 patients with thrombotic LIVCS from 9 hospitals. Moreover, these patients will be randomized to either the experimental group (rivaroxaban) or the control group (warfarin plus nadroparin). The primary outcome is stent occlusion rate. Secondary outcomes are quality of life scale survey results, all-cause mortality, anticoagulation-related mortality, and the proportion of participants with stent displacement/fracture, thrombosis, hemorrhage, and other vascular events.

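### If the true occlusion rates are equal at 20.2%, the planned 202 evaluable patients give about 42% power for non-inferiority, not the stated 80%

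*Protocol article*

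**What the plan says.** The Sample size calculation section of the protocol article gives one event rate, taken from a cited study: "stent occlusion rate of thrombotic LIVCS was 20.2"%. The design is a non-inferiority comparison of two groups, and the section states that "202 cases recruited in the study are enough under the power of 0.8, two-sided alpha level of 0.05, and the non-inferiority margin of 0.1". It continues: "We will include 224 samples in the study, taking into account a dropout rate of 10"%, and splits the 224 equally, 112 to each arm. The Abstract repeats the total: "We will recruit 224 patients with thrombotic LIVCS from 9 hospitals". The figure of 202 is therefore used as the evaluable total for both arms, that is 101 per arm. The article gives no separate expected rate for rivaroxaban and does not say whether the margin is an absolute difference.

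**The concern.** The calculation is printed with its inputs, so it can be checked without a statistical analysis plan. A common rate near 20% and a 10-point margin normally call for a few hundred patients per arm, and 101 per arm looks far too few. The primary outcome and the non-inferiority claim both rest on this figure. If the power is well below 80%, two equally effective regimens would more often than not give an inconclusive result, and readers would have been told to expect otherwise.

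**Working it through.** **Inputs from Sample size calculation.** Control rate 0.202; margin 0.10; power 0.80; two-sided alpha 0.05, which for non-inferiority means one-sided 0.025 (upper limit of the 95% CI below the margin); 10% dropout; 1:1 allocation.

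**Assumptions not printed.** The true rivaroxaban rate equals the control rate (varied in step 5). The margin is an absolute risk difference. A relative margin would be 0.1 × 20.2 = 2.0 points and would need far more patients, so it cannot explain 202.

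**1. Dropout step.** 202 / 0.9 = 224.4, which agrees with 224. This confirms that 202 is meant as the total.

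**2. Sample size at the stated inputs, equal rates.**
n per arm = (z₀.₉₇₅ + z₀.₈₀)² × 2p(1−p) / margin²
= (1.960 + 0.8416)² × 2 × 0.202 × 0.798 / 0.10² = 253.04, rounded up to 254.
The total is 508. With 10% dropout, 254 / 0.9 = 282.2, so 283 per arm and 566 enrolled. The Farrington-Manning formula gives 256 per arm. The stated total of 202 is not reproduced.

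**3. Power with the planned numbers, equal rates.**
SE at 101 per arm = √(2 × 0.1612 / 101) = 0.0565. Power = Φ(margin/SE − z).

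| Evaluable per arm | One-sided 0.025 | One-sided 0.05 |
|---|---|---|
| 101 | 42.5% | 55.0% |
| 112 (no dropout) | 46.2% | 58.7% |
| 202 | 70.7% | 80.5% |
| 254 | 80.2% | 87.7% |

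Simulating the confidence-limit test at 101 per arm and one-sided 0.025 gives 42.9%; Farrington-Manning gives 41.8%.

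**4. Precision.** The 95% CI half-width at 20.2% in both arms is 1.96 × 0.0565 = 11.1 points with 101 per arm, and 10.5 points with 112. Both exceed the 10-point margin, so identical observed rates at or near 20.2% would not show non-inferiority. This depends on the rate. The half-width equals 10 points when p(1−p) = 0.10² × 101 / (2 × 1.96²) = 0.1315, that is p ≈ 15.6%. With 101 per arm, identical observed rates below that would pass.

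**5. Power at 101 per arm if rivaroxaban is truly better** (control 20.2%, one-sided 0.025):

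| True rivaroxaban rate | Power |
|---|---|
| 20.2% | 42% |
| 18% | 60% |
| 16% | 75% |
| 15.2% | 80% |

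**6. Routes that lead to 202.**
- As a per-arm size, Farrington-Manning at one-sided 0.05 gives 201.5, rounded up to 202. The simpler unpooled formula gives 199.3, so 200.
- As a per-arm size, a two-sided superiority formula for 20.2% against 10.2% gives 202.
- As a total at the stated alpha, with a rivaroxaban rate of 15.2%: 7.849 × (0.1612 + 0.1289) / 0.15² = 101.2 per arm, or 202 in total to the nearest whole number per arm.

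**The case against.** The strongest reply is that the article condenses a fuller protocol and may have left out an expected rivaroxaban rate. A true rate of 15.2%, five points below control, gives 101.2 per arm at exactly the stated alpha, margin and power. On that reading nothing was miscalculated and one input is merely unprinted. This stands in part: the 42% is conditional on equal true rates, which is the usual planning assumption but not one the article states.

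It does not remove the point. The article prints a single rate and mentions no expected benefit, so a reader will take 80% to be the power under equal rates, and it is not. If a 5-point benefit was assumed, the claim of 80% depends on it and the text has to say so. A looser alpha does not rescue the figure either: one-sided 0.05 contradicts the stated level and still gives only 55%.

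Two stronger readings are tempting and not supported. A reader might infer that a per-arm number was mistaken for the total. The match at one-sided 0.05 is close, but it requires a different alpha from the one stated, and the 15.2% route fits about as well without any slip; the document does not choose between them. Nor would reading 202 as per-arm repair the plan, since that gives 71% power at the stated alpha. A reader might also infer that identical observed rates must always fail. That holds only at common rates above about 15.6% with 101 per arm.

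**Conclusion.** The point holds in conditional form. The printed inputs do not yield 202 evaluable patients in total. Under equal true rates of 20.2%, an absolute 10-point margin and one-sided 0.025, the planned total is 202/508, about 40% of what 80% power requires, and the power is about 42% (46% with no dropout). Only a materially better rivaroxaban rate, about 15.2%, brings the planned size to 80%, and none is stated. The arithmetic is secure; the origin of the 202 remains open. An 80% power claim on the primary outcome that its own printed inputs do not support must be corrected.

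**What to change.** In Sample size calculation, state the rivaroxaban rate that was assumed and that the test is at one-sided 0.025 (equivalently, a two-sided 95% CI), and say that the margin is an absolute difference. Then one of the following applies:

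- If equal rates were assumed and enrolment stays at 224, replace 80% with about 42% (46% with no dropout), and describe the primary result as an estimate of the difference with its 95% CI.
- If a better rivaroxaban rate was assumed, print it with its justification, and report the power under equal rates beside it.

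Both are wording changes. The cost is a less favourable stated power. Should the sponsor prefer to keep 80% power under equal rates, the consistent size is about 254 evaluable per arm, about 566 enrolled. That is the sponsor's choice and not part of the required correction. The Trial status section says recruitment had not begun, but its scheduled start of April 30, 2020 precedes the publication date of 2020-09-29, so a change in sample size may be harder than that section suggests.
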